**Figure 3 Fig3:**
[figure not shown]
**Telemedcare Clinical Monitoring Unit (CMU).**

### Data architecture

This study has complex data management and organisational requirements by virtue of its operation in five different location in five different states and territories, each with their own Ethics requirements and with different hospital systems from which to source hospital data. In this section we describe a secure and effective service-oriented approach for securely managing Telehealth services research data.

The data architecture and data integration services developed as part of this project make a considerable contribution to research and being in the public domain, warrant closer examination. A more detailed description has been published previously [27].

Data is being collected in this study from many different sources, in multiple formats and with varying levels of automation, with some requiring considerable manual processing. A simplified diagram of data sources used in this study is shown schematically in Figure 4 below.

**Figure 4 Fig4:**
[figure not shown]
**Schematic diagram of different data sources and their secure integration.**

 Entry and Exit Questionnaires are administered on line by PO’s when Test and Control patients are consented and are stored in OpenClinica Periodic Questionnaires (daily, weekly or monthly) are scheduled on the TMC clinician website and are presented and administered directly on the patient telemonitoring system. The results are stored in the TMC servers. Patient vital signs are recorded as longitudinal records and original waveforms are recorded and stored in the TMC server for quality control and diagnostic purposes. All records are accessible to the clinicians via the TMC clinician portal. Hospital Data is sourced from the Patient Administration Systems of hospitals servicing the trial sites and is supplied in the format of the Hospital Roundtable [28]. This comprehensive data set is requested for four years prior to enrolment and for the duration of the trial. MBS Data available from the Department of Human Services following Ethics Approval. This provides a comprehensive record of all primary care services provided under the national health insurance scheme PBS Data available from the Department of Human Services following Ethics Approval. This provides a comprehensive record of all medications dispensed under the national health insurance scheme. MBS and PBS Data is available for a total of 4.5 years prior to and including the duration of the trial. HIE Data from focus groups and structured interviews are transcribed and annotated before storage in OpenClinica.

Technical details on the data architecture designed to provide secure Role Based Access Control to de-identified patients data for research and analysis has been previously reported [27].

### Questionnaire instruments

A number of questionnaire instruments were developed or adapted from the literature for use in the trial. All Patients enrolled in the study were required to take an Entry and Exit Questionnaire. This questionnaire instrument was developed from a base CSIRO CAFHS Human Research Ethics Standard Screening Medical Questionnaire [29] with the addition of other questionnaire instruments either wholly or in part, measuring demographic, lifestyle, health and disease characteristics. Key elements of the Entry and Exit Questionnaires are described in Table 3 below.

In addition to the Entry questionnaire, a number of questionnaires are scheduled and administered during the trial with varying frequency. These are described in Table 4 below.

**Table 4 Tab4:** **Questionnaire Instruments and their schedule**

Questionnaire	Administering schedule
COPD (Developed by the Austin Hospital)	Daily
CHF (Developed by the Austin Hospital)	Daily
EQ-5D (Quality of life)]	Weekly
Kessler 10 (Mental health)	Monthly
heiQ – selected domains (Self monitoring, Health services navigation and Social isolation)	Entry, 6 months, Exit
Morisky medicine adherence scale	Entry, 6 months, Exit

### Data models

As described earlier, patient data is obtained from multiple sources and integrated into a single unified database linked via the unique OpenClinica ID (OCID). A Data Model has been developed which provides the template for data analysis by linking outcomes and objectives to specific data variables and identifying the data sources. This data model underpins nearly all quantitative analysis presented in this report. The data model is presented below in Table 5.

**Table 5 Tab5:** **Data Model for evaluating outcomes and objectives**

Objective/outcome	Data variable	Data source
Define the study cohort/confirmation of selection critera and exclusions	Admitted to hospital for their condition at least twice in the previous year, or ≥ 4 times in previous five years	Hospital health roundtable records - obtained from local hospital for previous five years.
		• Date admitted
	Exclusions are mental health and cancer patients	• Date discharged
		• Reason for admission (ICD 9/10 Codes)
		• Procedures carried out
Establish if telehealth	Number of unscheduled admissions to hospital for their condition	MBS Flag (In hospital) Health roundtable record
Improves patient outcomes/reduced hospitalisation		• Date admitted
		• Date discharged
		• Reason for admission (ICD 9/10 Classification)
		• Medication administered
		• Procedures carried out
Establish If telehealth improves patient outcomes/reduced use of clinical services (Impact on clinical workforce availability and deployment)	Number of visits to/by GP	MBS records
	Number of visits to/by specialists	MBS records
	Number of visits by community nurse	MBS records
	Number of visits to/by allied health (ie occupational therapist)	MBS records (If reimbursable from Medicare)
	Changes in prescription history	PBS
	Communication with CCC	CCC Logs from CSIRO Portal
Organisational change management and impact on workplace culture	Administrative/operational changes implemented/required in order to implement the Telehealth service.	Questionnaires and structured interviews.
		• Within first three months
		• Every six months thereafter
Useability of monitoring equipment	Compliance with monitoring schedule, recorded daily.	TMC Logs
	Extra measurements taken by patient (When? Which?)	TMC Logs
	Compliance with questionnaire administration (When? Which?)	TMC Logs
	Use of video conferencing	TMC Logs
	Overall data usage	iiNET provided logs
Useability/acceptability	Ease of use	Questionnaires delivered via TMC
For patients of monitoring Equipment	Quality of training received	• One month after first deployment
	Patient embarrassment if visitors know they are being monitored	• Midpoint of trial
	Acceptability as an item of furniture	• At end of trial
	Easy or hard to take measurement	
	Important/not important in patients' self management	
	Responsiveness of clinical care coordinator in responding to changes	
	Quality of training received	
	Patient embarrassment if visitors know they are being monitored?	
	Easy or hard to take measurement	
Carers experience with telehealth (Community nurse/carer)	Ease of use of (i) equipment and (ii) Clinician website	Questionnaires and structured interviews of community nurses
	Changes to previous clinical models of care	• One month after first deployment
	Effectiveness in improving ability to deliver care	• Midpoint of trial
	Impact on workload	• At end of trial
Carer's experience with telehealth (Relative or other carer)	Effect on carer stress	Questionnaires and structured interviews
	Effect on carer workload	• At first deployment
	Effectiveness in improving ability to deliver care	• Midpoint of trial
	Access to clinician web site	• At end of trial
Gp experience with telehealth	Ease of use	Questionnaires and structured interviews of Patients' GP
	Changes to clinical models of care	• Within 3 months of first deployment
	Effectiveness in improving ability to deliver care	• Midpoint of trial
	Impact on workload	• At end of trial
Useability, acceptability of clinician web interface	Ease of use?	Questionnaires and structured interviews
	Quality of training received	• One month after first deployment
	How many hours required	• Midpoint of trial
	Value and ease of use of Video conferencing	• At end of trial
Health economic outcomes	Daily cost of hospitalisation	Health roundtable data
	Cost of procedures carried out whilst in hospital	Health roundtable data
	Cost of visits to/by GP	MBS Data
	Cost of visits to/by Allied Health (ie Chiropodist or OT)	MBS Data
	Cost of visits by community Nurse/carer	MBS Data
	Cost of travel to GP	MBS Data
	Loss of earnings if patient is still employed, from days taken off for illness or visits to health professionals	Use Google Maps to determine distance travelled from home address to address of service location, then apply standard costing model. Ie flag fall + km charge.
		Estimate from patient salary and time spent on each visit
Cost of delivering telehealth services	Cost of clinical care coordinator(s)	Health service provider and logs recorded
	Cost of clinical nurses/carers	Health service provider and logs recorded
	Cost of providing network services	iiNET billing at commercial rates
	Cost of providing Telehealth monitoring services	TMC commercial daily subscription costs
	Depreciated costs of capital equipment	Our own project records
	Estimate of cost of space for monitoring centre at each site	Estimates from Health service Provider

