 Demonstrate and document how telehealth services can be successfully deployed across Australia, by piloting services in five different settings across five states with a range of health service provider’s, including Local Health Districts, Medicare Locals and not for profit community organisations. This will be demonstrated by deploying and demonstrating the operation of Telehealth monitoring in a multi-site multi-state case matched control trial (Before-After-Control-Impact (BACI) design) of chronically ill patients living in their own homes in the community. This has never previously been attempted in Australia. Provide the clinical and health economic evidence on how Telehealth services can be scaled up nationally to provide an alternative cost effective health service for the management of chronic disease in the community. Provide evidence that at home telemonitoring has the potential to reduce unscheduled admissions to Accident and Emergency (A&E) compared to the control group. Provide evidence for an impact on hospital admissions, mortality, clinical events and symptoms and improvements in functional measures and patients' and carers’ experiences with care. Evaluate health economic benefits Evaluate impact on clinical work force availability and deployment Evaluate impact of human factors (acceptability, usability by patients, carers, nurses, GPs and administrators, impact on workplace culture) Evaluate impact of workplace culture Evaluate impact of organisational change management and business processes Develop a new evidence based data analytical technique for the risk stratification of patients’ health status daily and demonstrate that this facilitates the management of large numbers of patients by orchestrating an optimal and timely allocation of resources to avoid unnecessary hospitalisation

For each of the above objectives, operation of the trial at five different sites representing a range of different models for the management of chronic disease in the community will allow the identification and analysis of site specific differences in workplace culture, organisational change management and staff and management capabilities that contribute to differences in measured health, social and economic outcomes.

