Following the signing of a consent form and completion of the Entry Questionnaire, Test patients are connected to the internet and supplied with the TMC Telemonitoring system and trained on its use by the Project Officer (PO) at each site. Their vital signs and questionnaire responses are subsequently monitored on a daily basis by the Clinical Care Coordinator (CCC). On site visits and technical support as well as the obtaining of Consent and the administration of Exit questionnaires are the responsibility of the PO.

Control patients also complete the Entry questionnaire but otherwise continue to receive normal care. For each intervention participant, as many as six control candidates are automatically case matched on gender, age, chronic condition and Socio-Economic Indexes for Areas (SEIFA) [24]. On their consent the two closest matching control candidates commence as participants in the study. The remaining four candidates are held in reserve. Table 2 below demonstrates the case matching process.

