## Abbreviations

ADSL: Asymmetric digital subscriber line
ADSL2: Asymmetric digital subscriber line - 2^nd^ specification
CCC: Clinical Care Coordinator
CDM: Clinical Data Management
CHD: Coronary heart disease
CHF: Congestive heart failure
CMU: Clinical Monitoring Unit
COPD: Chronic obstructive respiratory disease
CSIRO: Commonwealth Scientific and Industrial Research Organisation
CTC: Clinical Trial Coordinator
EDC: Electronic data capture
HREC: Human Research Ethics Committee
LHD: Local Health District
MBS: Medical benefits scheme
NBN: National broadband network
PAS: Patient administration system
PBS: Pharmaceutical benefits scheme
PCEHR: Personally controlled electronic patient record
PO: Project Officer
SEIFA: Socio-economic indexes for areas
TMC: Telemedcare telemonitoring devices/services
VDSL: Very-high-bit-rate digital subscriber line.

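### Patient acceptability of the telemonitoring unit is collected only on the unit itself, so patients who stop using it are likely to be missing from the midpoint and end-of-trial results

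*Protocol article*

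**What the plan says.** The project objectives (Aims and objectives) include: "Evaluate impact of human factors (acceptability, usability by patients, carers, nurses, GPs and administrators, impact on workplace culture"). In Table 5 (Data models), the row on useability and acceptability of the monitoring equipment for patients covers ease of use, training, embarrassment, acceptability as furniture, ease of measurement, importance for self-management and the care coordinator's responsiveness. Its only source is "Questionnaires delivered via TMC", with three time points: one month after first deployment, midpoint and end of trial. The abbreviation list reads "TMC: Telemedcare telemonitoring devices/services".

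The Data architecture section says that periodic questionnaires "are presented and administered directly on the patient telemonitoring system. The results are stored in the TMC servers". After a further sentence on vital signs and waveforms it adds: "All records are accessible to the clinicians via the TMC clinician portal". Selection of trial participants says that the Clinical Care Coordinator monitors vital signs and questionnaire responses daily. It then says of the Project Officer: "On site visits and technical support as well as the obtaining of Consent and the administration of Exit questionnaires are the responsibility of the PO". The Project Officer also trains the patient on the unit.

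The Exit questionnaire is required of all enrolled patients and is stored in OpenClinica. Its key elements (Table 3) include no acceptability instrument.

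**The concern.** Whether a patient answers at midpoint or end of trial depends on still having and using the unit. Continued use may in turn depend on what the items ask: whether the unit is easy to use, embarrassing or welcome in the home. Respondents at the later waves would then be a selected group. The intervention runs for 6 to 18 months (Classical BACI designs and extensions), so there is time for selection to build up after the one-month wave.

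The trial is meant to inform national deployment, and the views of patients who gave the equipment up are evidence a policy maker would want. The other user groups in Table 5 (community nurses, relatives and other carers, GPs, users of the clinician website) have structured interviews as well as questionnaires. The patient row has only the device.

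A second, separate matter is that one item rates the care coordinator. If that coordinator can read the answer, patients may be reluctant to mark it low.

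**Working it through.** **No plan figure to reproduce.** The article states no acceptability rate, stopping rate or precision for this outcome. The one related figure checks: 5 sites × 25 = 125 Test patients.

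**Is there another patient route?**
- Exit questionnaire: off the device and given to everyone, but Table 3 lists no acceptability items.
- Focus groups and structured interviews (Data architecture): mentioned, but patients are not named as participants, and the patient row of Table 5 lists none.
- Compliance logs (Table 5, the row directly above): these record use of the unit daily, so they show that a patient stopped. They hold no ratings or reasons, and Table 5 does not link them to the acceptability result.

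No off-device measure of patient acceptability is therefore stated.

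**Size, by illustration.** Let d be the share of Test patients who stopped and do not answer, p_u the proportion of continuing users who find the unit acceptable, and p_s the same proportion among stoppers. All three are assumptions.

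Reported = p_u. True = (1 − d)·p_u + d·p_s. Overstatement = d·(p_u − p_s).

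With p_u = 85%:

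| d | respondents of 125 | p_s = 85% | p_s = 65% | p_s = 45% | p_s = 25% |
|---|---|---|---|---|---|
| 10% | about 112 | 0 | 2 | 4 | 6 |
| 20% | 100 | 0 | 4 | 8 | 12 |
| 30% | about 88 | 0 | 6 | 12 | 18 |

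Entries are percentage points. With p_u = 90%, p_s = 20% and d = 30%, the overstatement is 0.30 × 0.70 = 21 points.

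For scale, at d = 20% the standard error of the reported proportion is √(0.85 × 0.15 / 100) = 3.6 points, so a 20-point gap already gives a bias of about one standard error (4 points).

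The sign can also reverse: with p_u = 65%, p_s = 85% and d = 20%, the reported figure is 0.20 × 0.20 = 4 points too low.

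**Bounds without assuming p_s.** With 85% of respondents positive and 20% silent, the proportion among all 125 lies between 0.80 × 85% = 68% and 68% + 20% = 88%. The on-device data cannot narrow this range.

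**The case against.** The strongest reply is the adjacent row of Table 5. Rejection by disuse is recorded daily in the compliance logs without the patient having to answer anything. A reader might infer that the trial could report high acceptability while a sizeable minority's rejection of the unit stays hidden. The document does not support that: the stopping will be visible. What is lost is narrower, namely the stoppers' ratings and reasons.

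Nor is it established that the result is biased upward. In a cohort aged 50 and over with repeated admissions, patients may stop because of death, a long hospital stay or a move, and not from dislike. If stoppers rate the unit as users do, the bias is zero.

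A reader might also take it as stated that the coordinator reads these answers. The sentence on portal access follows one on vital signs and waveforms. The questionnaire sentence concerns daily, weekly or monthly instruments, and the acceptability questionnaire is not in Table 4. Access is plausible, given that the coordinator monitors questionnaire responses daily, but it is not stated. It would bear mainly on one item, and it has nothing to do with stoppers going missing.

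Finally, a condensed article may leave follow-up of stoppers to the full protocol. That stands in part. But Table 5 is presented as the template for analysis and fixes the route for this outcome, and no off-device route for patients appears elsewhere in the article.

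**Conclusion.** The point holds in a limited form. Table 5 ties patient acceptability to the device being rated, so patients who stopped are likely to be missing at midpoint and end of trial. The one-month wave is least affected.

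The direction rests on the assumption that stoppers like the unit less. The size rests on an unknown stopping rate and an unknown gap: from 0 points with no gap to about 18 to 21 points with 30% stopping and a gap of 60 to 70 points. Possible courtesy bias on the coordinator item is a separate and smaller matter, conditional on portal access. Utilisation and cost outcomes are not affected. The change is worth making because acceptability is a named objective and the remedy is cheap.

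**What to change.** - Keep the on-device questionnaires at all three time points.
- Add the Table 5 acceptability items (about seven) to the existing off-device Exit questionnaire, for every Test patient who received a unit, including those who stopped or returned it.
- Have these items self-completed. The Project Officer trained and supported the patient, so asking them face to face would invite the same courtesy bias on training and ease of use.
- Store the answers in OpenClinica, outside the clinician portal.
- Report acceptability with all Test patients who received a unit as the denominator, with stoppers shown separately, the number not answering stated, and the compliance logs alongside.

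The cost is one additional OpenClinica form and a few extra minutes per Test patient at Exit. Some stoppers may still not respond, so the change reduces the selection but may not remove it.

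### Community-nurse and GP workload and model-of-care items have no wave before deployment, and the carer and organisational first waves are not clearly placed before it

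*Protocol article*

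**What the plan says.** Table 5 sets the measurement times for staff, carer and organisational outcomes.

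- **Community nurses.** The items include "Changes to previous clinical models of care" and effect on workload. The first wave is "One month after first deployment", followed by the midpoint and end of the trial.
- **GPs.** The items include changed models of care and effect on workload. The first wave is "Within 3 months of first deployment", followed by the midpoint and end of the trial.
- **Relatives and other carers.** The items include "Effect on carer stress" and effect on carer workload. The first wave is "At first deployment", followed by the midpoint and end of the trial.
- **Organisation and workplace culture.** The listed variable is the administrative and operational change made or needed to introduce the service. The first wave is "Within first three months", then "Every six months thereafter".

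The section Data models presents Table 5 as the template for nearly all the quantitative analysis. Aims and objectives asks what the new service does to normal care delivery and how existing practice evolves, and it lists staff and carer workload and strain among the research topics.

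**The concern.** A statement that a service changed workload or a model of care needs the state before the service began. If the first answer comes one month or more after the start, two routes remain. Respondents can recall how things were, while already using the system. Or later waves can be compared with an early wave that may itself reflect set-up and training. If set-up load is high in that early wave, a later fall could be read as telehealth reducing workload.

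Aims and objectives also wants site differences in culture and staff capability to help explain differences in outcome. That is harder if what existed at a site beforehand was not recorded separately from what the service brought. An analysis plan cannot repair this later, because the earlier state at a site can no longer be observed once units are in use.

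**Working it through.** No sample size, power or error-rate figure bears on this point, so the check sets the first measurement time of each row beside what a change measure would need.

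| Row of Table 5 | First wave | Value before the start? |
|---|---|---|
| Community nurse: workload, model of care | "One month after first deployment" | No |
| GP: workload, model of care | "Within 3 months of first deployment" | Not assured |
| Relative or other carer: stress, workload | "At first deployment" | Only if asked before connection and training |
| Organisation and culture | "Within first three months" | Not stated; the starting event is not named |
| Workforce availability: visit counts | Medicare (MBS) records | Yes |

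1. **Nurses.** The first wave is fixed after the start, so no baseline exists for these self-reports.
2. **GPs.** The wave is a window. Nothing requires any part of it to fall before the start, and the same wave asks about ease of use, which presupposes use. The article also does not say whether deployment means the first unit at the site or the unit of that GP's own patient, so what the first GP wave represents may differ between GPs.
3. **Other sources.** The Entry Questionnaire is described for Test and Control patients only. No entry form for nurses, GPs or carers is named, and no comparison group of staff or carers is described.
4. **Contrast with patients.** Under Selection of trial participants, Test patients complete the Entry Questionnaire before they are connected. Table 4 schedules the heiQ and Morisky instruments at entry, six months and exit. The order is clear for patients and is not carried over to staff and carers.
5. **Count.** Two groups (nurses, GPs) × two items (workload, model of care) = 4 items without an assured starting value. Two further rows (carers, organisation) have a first wave whose place relative to the start is open.
6. **What has a before period.** Table 5 maps workforce availability and deployment mainly to MBS visit counts, with prescription records and care-coordinator logs. The Data architecture section gives 4.5 years of MBS and PBS data, trial included.

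**The case against.** The strongest reply is that these rows were never meant as before-after endpoints. BACI is defined for matched Test and Control patients. The staff and carer rows concern experience with telehealth, use questionnaires and structured interviews, and may ask directly about perceived change. Some items, such as ease of use, training and perceived effectiveness, cannot be answered before use. This stands for those items, and they should stay where they are. It does not cover current workload or the current model of care, which can be asked beforehand. Perceived change is a legitimate result if it is called that.

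A second reply is that the earlier state is partly known. Sites were chosen for their differing models of care, Control patients continue under the existing model, and the existing model of care is a named research topic. That helps describe the site. It gives no starting value for an individual nurse's or GP's workload or practice. A full protocol might contain such a wave, but the article does not mention one.

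It is also fair to say that a start-up peak in workload is a possibility which the documents do not report.

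Two stronger readings are tempting and are not supported:

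- **That every workforce, culture and carer outcome lacks a baseline.** The objective "Evaluate impact on clinical work force availability and deployment" is served mainly by MBS visit counts, which have a before period. The carer wave is at time zero and may be a usable baseline. The organisational row has no stated starting event and records implementation changes, so its defect is ambiguity.
- **That the first GP wave can collide with the midpoint wave at month 3.** This halves the shortest intervention (6 / 2 = 3 months). Table 5 refers to the midpoint of the trial, and interventions may last up to 18 months (18 / 2 = 9 months), so the two clocks differ.

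**Conclusion.** The point holds for self-reported workload and model of care among community nurses and GPs. Four items have no assured value from before the service, with the first wave at one month for nurses and up to three months for GPs. For carers and organisations the finding is narrower: the article should say whether the first wave precedes the start.

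The conclusion assumes that Table 5 lists all the waves for these rows and that the GP window runs forward from deployment, which is its natural reading. The direction and size of any bias cannot be derived from the documents. The change is worth making because these are stated objectives and the before state is lost once a site starts. The visit-count measures of workforce use and the BACI analyses of utilisation and cost are not touched.

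**What to change.** Split the first wave by type of item.

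- **Nurses:** collect current workload and current model of care before the first unit is installed at their site.
- **GPs:** collect the same items before that GP's first Test patient is connected. A site-wide date would not work, because the respondents are the GPs of enrolled patients and some may not be known when the site starts.
- **Carers:** state that the stress and workload items are taken before connection and training.
- **Organisation:** name the starting event and place the first wave before first installation.
- **Unchanged:** ease of use, training and perceived effectiveness stay at their present times.
- **Reporting:** give impact as change from the value before deployment. Where none exists, including at sites already running, label the result as perceived or recalled change.

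Questionnaires and interviews for these groups are already planned. The cost is one short extra contact for nurses and GPs; for carers and organisations it is a matter of order and wording.

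### Table 5 costs patient travel for GP visits only, which is narrower than the stated aim on patient-borne costs and leaves avoided hospital trips without a travel saving

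*Protocol article*

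**What the plan says.** The cost-effectiveness question in Aims and objectives asks for changes in costs that fall on patients. It does not restrict this to one type of service.

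The section Data models presents Table 5 as the framework for nearly all of the quantitative analysis. Under health economic outcomes, the only travel item in that table is "Cost of travel to GP". The rule for it reads "Use Google Maps to determine distance travelled from home address to address of service location, then apply standard costing model", followed by "Ie flag fall + km charge".

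Other services appear in Table 5 without a travel item. Hospital use enters as "Daily cost of hospitalisation" and the cost of procedures. Allied health enters as a visit cost, and specialists enter as "Number of visits to/by specialists". The other patient-borne item in the same block is wider in scope: "Loss of earnings if patient is still employed, from days taken off for illness or visits to health professionals".

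**The concern.** Two costs of the same trip, the fare and the lost working time, have different scopes in one table. Lost time counts for a visit to any health professional, but the fare counts only for a visit to a GP. The fare item is also narrower than the research question it serves.

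The gap falls where the trial expects its effect. Table 1 selects patients for repeated unplanned admissions (at least 2 in 12 months or at least 4 in 5 years), and the stated expectation is fewer unscheduled hospitalisations. The trips that the intervention is meant to prevent have no travel price, whereas GP trips do. The omission is therefore not a constant that cancels between Test and Control patients. It removes a component that should differ between them if the intervention works.

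**Working it through.** The plan gives no travel-cost figure, so there is nothing to reproduce. The check compares scopes first and then illustrates the size.

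**Scope, item by item**
- GP: visit counted, visit costed, travel costed.
- Specialist: visit counted, no travel item.
- Allied health: visit counted, visit costed, no travel item.
- Hospital: admission counted, stay and procedures costed, no travel item.
- Loss of earnings: visits to any health professional.
- Research question: patient-borne costs in general.

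**Inputs for the illustration (all assumed)**
Flag fall F = $4; charge c = $2 per km; GP at 5 km, 12 visits a year; hospital at 20 km, 2 admissions a year. Each return trip is two legs with a flag fall on each, so its cost is 2(F + c·d).

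**Share of travel cost captured**
- One GP return trip: 2 × (4 + 2 × 5) = $28. Twelve trips: 12 × 28 = $336.
- One hospital return trip: 2 × (4 + 2 × 20) = $88. Two admissions: 2 × 88 = $176.
- All travel: 336 + 176 = $512. GP-only share: 336/512 = 0.66.

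This share does not depend on how many legs are priced, provided all services are treated alike. With one leg each, it is 168/(168 + 88) = 168/256 = 0.66.

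**Sensitivity to assumed trip counts and costs (12 GP trips, return-priced)**
- 6 other trips at the same cost per trip: 12/18 = 0.67.
- 12 other trips at the same cost per trip: 12/24 = 0.50.
- 12 other trips at three times the cost per trip: 12/(12 + 36) = 0.25.
- Base case, but the patient pays only the leg home from hospital: 336/(336 + 2 × 44) = 336/424 = 0.79.

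**Possible change of sign**
Suppose telemonitoring leads to one admission fewer and two GP visits more.
- All trips priced: −88 + 2 × 28 = −$32, a saving.
- GP trips only: +2 × 28 = +$56, a loss.

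On these inputs one hospital trip equals 88/28 = 3.1 GP trips. One to three added GP visits per avoided admission would therefore turn a true travel saving into an apparent loss.

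**The case against.** The strongest objections concern the text and the materiality.

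- **Table layout.** In the text at hand the rows are shifted: the map rule sits beside the earnings item, and the rule speaks of a service location in general, not of a GP practice. The authors may have meant all services. That is possible, but the only travel variable names the GP, and a data model is followed by its variables.
- **Materiality.** Travel is not among the variables in Table 6 or the example outcomes of the mixed model. It is one component of one economic question. This stands and limits the weight of the point.
- **Hospital fares.** The documents do not say that patients pay for both legs of an admission. This also stands; if they pay for only one leg, the omission shrinks (0.79 in place of 0.66 above).
- **Shift of care.** No part of the article predicts a move from hospital to GP. The change of sign is therefore conditional. An understated saving needs only fewer hospital trips, which the article does expect.

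Two stronger readings are tempting. First, a reader might infer that the rule prices the outward leg only, so that each GP trip is costed at about half. The text says how distance is measured and leaves the number of legs to an unspecified standard costing model. The captured share would be 0.50 with a flag fall per leg, 0.51 to 0.81 with a single flag fall (assumed F $3 to $5, c $0.75 to $2.00, 2 to 40 km), and 1.00 if the model already covers the return. A common factor would also leave the relative change in GP travel cost intact. Second, a reader might infer that GP home visits attract a flag fall, because visits are counted as "Number of visits to/by GP". The travel item is labelled only as travel to the GP, so nothing sends home visits through the rule.

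**Conclusion.** The point holds on scope. Table 5 costs patient travel for GP visits alone, against a research question on patient-borne costs in general and an earnings item that covers all health professionals. Travel to hospital, specialists and allied health is left at zero, including the trips the intervention aims to avoid.

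Under the assumed base case the GP-only item captures 66% of GP and hospital travel cost. The other assumed mixes give 25% to 79%. These figures show the order of size only, since the article states no rates, distances or trip counts. A change of sign requires care to move from hospital to GP. The documents do not support a claim that GP trips are costed at half; they leave the return leg open, and it should be stated.

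**What to change.** Reword the travel row of Table 5 so that it covers every visit the patient makes to a GP, specialist, allied-health provider or hospital, using the same distance method and costing model for all of them and identically for Test and Control patients. State in the same row that the outward and return legs are both priced.

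The visits are largely in data the trial already collects, namely the MBS records and the hospital records. Allied-health visits not reimbursed by Medicare are an exception, as Table 5 itself implies. The cost is a little more analysis work for the extra distance look-ups, and a stated convention for any hospital leg that the patient does not pay for.
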